### **3.5.3 Inclusion and exclusion criteria**

The inclusion criteria for participation in the education program are:

- 1) The respondents aged 60 years or more
- 2) The respondents have been diagnosed with diabetes (old or new)
- 3) The respondents presented with or without diabetic foot problems
- 4) The respondents must be Malaysian.
- 5) The respondents who are able communicate sufficiently well (Malay) to understand the education program.
- 6) The respondents who are able to perform activity daily living independently (e.g., bathing, feeding, grooming etc.). The information will be gathered from the the screening process.
- 7) The respondents who have no major complications which would interfere with foot self-care behaviour (such as blind and stroke).

The specific exclusion criteria are:

- 1) Respondents who are currently has been diagnosed with mental health problem such as Schizophrenia, Bipolar Disorder and Alzheimer disease. The information will be gathered from the RSKs' health record unit.
- 2) Respondents who are having impaired in cognitive level. The information will be gathered from the screening process.
- 3) Respondents who are having depression. The information will be gathered from the screening process.

## 3.6 Instruments

### 3.6.1 Questionnaire

The questionnaire will be prepared in English and Malay language. Respondents need to answer the questionnaire independently if they were able to read and write. Interview will be conducted only for those illiterate respondents. The information that will gathered to answer objectives of the study the respondents are as follow;

Section A is demographic data. The information required are about age, ethnicity, gender, education level, marital status, number of children, frequency of being visited by children/ relatives and friends and duration of stay in RSK.

Section B is clinical characteristics. The data will gather about FBS level, duration of diabetes, treatment of diabetes, other disease (except diabetes), smoking status, hospitalization due to diabetes problem and previous diabetes education received.

Section C measure on foot self-care behaviour. The Diabetes Foot Self-Care Behaviour Scale (DFSBS) (Chin & Huang, 2013) will be adapted in this study. The DFSBS contains 16 items. The scale had two parts: In the first part, the responses will be rated on the number of days patients performed a certain behaviour over the course of one week (0 for never, 7 for every day they performed the activity). In the second part, the responses will rated by the frequency with which patients performed a certain behaviour in general, from never (0) to always (5). The responses will be rated as a 5-point Likert scale [never/ 0 day per week (1), rarely/ 1-2 days per week (2), sometimes/ 3-4 days per week (3), often/ 5-6 days per week (4) and always/ 7 days per week (5)] (Chin & Huang, 2013). A higher score indicated good foot self-care behaviour.

Section D is measure on foot care self-efficacy (foot care efficacy expectation). The Foot Care Confidence Scale (FCCS) (Sloan, 1998) will be adapted to this study. The instrument is a public domain. There are 12 items measuring on self-confidence in managing foot care. The scale given into five scores; strongly not confident (score 1) to strongly confident (5). Higher scores shows high in self-confidence in managing foot care behaviour.

Section E is measure on foot care outcome expectation (FCOE). Content of the question that will be constructed must suit with education package, focus on diabetes foot complications and risk factors and the foot care for elderly with diabetes. The questionnaire will be developed based from previous literatures (Resnick, Zimmerman, Orwig, Furstenberg, & Magaziner, 2000; Lenz & Shortridge-Baggett, 2002; Chlebowy & Garvin, 2006; Wu et al., 2008; Kakudate et al., 2011; Kedem, Evans, & Chapman-Novakofski, 2014). There have six items and the scale consists of five scoring; strongly disagree (1) to strongly agree (5). Higher scores shows high in self-confidence that a foot behaviour will have the desired effect.

Section F is measure on knowledge on foot care (KFC). Content of the questions that will be constructed must suit with education package, focus on diabetes foot complications, risk factors and the foot care for elderly with diabetes in Malaysian setting. The questionnaire will be developed based from previous literatures (Pollock et al., 2004; Desalu et al., 2011; Eigenmann et al., 2011; Morey-Vargas & Smith, 2015;

American Diabetes Association, International Diabetes Federation, Clinical Practice Guideline, National Diabetes Institute, Malaysian Diabetes Association). In this section, the elderly needs to answer 11 questions with three answer choices (true, false, don't know). Each correct answer will be given 1 point. The cut-off point of this questionnaire are good (score  $\geq 70\%$ ), satisfactory (score 50-69%) and poor (score  $<50$ ) (Desalu et al., 2011). On the other hand, the score ranged from 0 to 11. A higher score indicated a good level of knowledge of foot care.

Section G is measure on quality of life. Neuropathy and Foot Ulcer Specific Quality of Life (FS-QOL) (Vileikyte et al., 2003) will be adapted in this study. These 27 items asked about the effect of foot issues may have on daily life and well-being. Patient need to recall (in the past 4 weeks) about their feeling, experienced the foot issue symptoms how foot issues affect their daily activities, relationships and feelings. This is Likert scale measures in several categories; (all the time, sometime, never), (very much, somewhat, not at all) and (agree, neither agree or disagree, disagree). The instrument measured should therefore include items 1-13 (symptoms) and 14-27 (psychosocial functioning). Thirteen items assess specific somatic experiences in three domains: i.e., Pain (items 1-7), Lost/reduced feeling (items 8-10); and Diffuse sensory-motor symptoms (items 11-13). Specific functional, social and emotional experiences are assessed in three domains with an additional 14 items: Restrictions in activities of daily living (items 14 – 16), and Disruptions in social relationships (items 17-20), and Emotional distress (items 21- 27). The frequency of these experiences, somatic, social and effective, are reported on 3 point scales (never, sometime, all the time). A participant's score for a domain is the mean of the items in that scale with higher scores representing more severe symptoms or greater disruption in functioning.

For each of these 27, specific items, patients are asked to judge the degree to which the somatic experience, restriction of activities, social function and emotional states have been a bother and/or important to them (Vileikyte et al., 2003). The bother /importance items were scored as 1=none; 2= some; 3= very. Weighted scores were calculated by multiplying the scale score by the corresponding bother/importance score (Vileikyte et al., 2003). Multiplying the frequency of experience by its bother and importance provides a more detailed picture of the degree to which the specific experience impacts satisfaction or quality of life (Vileikyte et al., 2003).

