### Part F: Knowledge on foot care

The questions below ask about your knowledge on foot care. Please **circle** in an appropriate answer.

| People with diabetes should.....                                                       | Answer |       |            | Remark |
|----------------------------------------------------------------------------------------|---------------|-------|------------|---------------|
| 1. take medication regularly because they liable to get diabetes complication          | True          | False | Don't know |               |
| 1. look after their feet because they are more liable to get infection (true)          | True          | False | Don't know |               |
| 2. look after their feet because they may not feel a minor injury to their feet (true) | True          | False | Don't know |               |
| 3. look after their feet because wounds and infection may not heal quickly (true)      | True          | False | Don't know |               |
| 4. look after their feet because they may get a foot ulcer (true)                      | True          | False | Don't know |               |
| 5. not smoke because smoking causes poor circulation affecting the feet (true)         | True          | False | Don't know |               |
| 6. check their feet daily (true)                                                       | True          | False | Don't know |               |
| 7. treat themselves if they found redness/ bleeding between their toes (false).        | True          | False | Don't know |               |
| 8. Tell doctor if they have corn/ hard skin lesion                                     | True          | False | Don't know |               |
| 9. wash their feet daily (true)                                                        | True          | False | Don't know |               |
| 10. check temperature of the water before wash their feet to avoid injury (true)       | True          | False | Don't know |               |
| 11. check inside of their shoes only when necessary (false)                            | True          | False | Don't know |               |

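### Most knowledge items are keyed 'true', so ticking 'true' throughout is classed as good knowledge; the class cannot tell agreeing from knowing, and the total score does so only weakly

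*Combined protocol and SAP*

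**What the plan says.** Section 3.6.1 (Section F) describes the knowledge scale: "the elderly needs to answer 11 questions with three answer choices (true, false, don't know"). On scoring it says "Each correct answer will be given 1 point"; no deduction for a wrong answer is mentioned. It then sets the bands: "The cut-off point of this questionnaire are good (score $\geq 70\%$ ), satisfactory (score 50-69%) and poor (score $<50" per cent. The text adds that "the score ranged from 0 to 11" and that "A higher score indicated a good level of knowledge of foot care".

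The form itself (Part F: Knowledge on foot care) prints the key beside most rows. Only two rows are keyed false: item 7, "treat themselves if they found redness/ bleeding between their toes (false"), and item 11, "check inside of their shoes only when necessary (false"). Every row offers 'don't know'.

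Knowledge is a secondary outcome (sections 2.6 and 3.10). Table 3.5 reports it as mean (SD) and n (%), and compares the arms over the three time points by mixed ANOVA. For this scale, section 3.6.2.1 plans face and content review, a content validity ratio and Cronbach's alpha.

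**The concern.** When nearly every correct answer is the same word, a habit of agreeing earns almost the same credit as knowledge. That matters here because section 3.6.1 attaches a verbal label to the score and Table 3.5 plans counts and percentages, so a resident with no knowledge can be reported as having good knowledge.

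The setting makes agreeing credible. Residents may have little schooling, and the researcher interviews those who cannot read or write. That researcher knows the allocation (section 3.3) and gives the intervention arm repeated encouragement (section 3.7.1).

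None of the planned checks looks at the balance of the key. Content review asks whether each item is essential. Alpha can even rise when people agree consistently across items keyed the same way.

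**Working it through.** **Step 1. Count the items.** Section 3.6.1 states 11 questions. The form prints 12 rows, because the number 1 is used twice, so the stated 11 is not reproduced. The rows are:

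- keyed true: the second row numbered 1, and items 2, 3, 4, 5, 6, 9 and 10, which makes 8;
- keyed false: items 7 and 11, which makes 2;
- no key printed: the first row numbered 1 (taking medication) and item 8 (telling the doctor about corns), which makes 2. Both read naturally as true.

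**Step 2. Score a resident who ticks 'true' on every row.** Score = items whose answer is true / items scored. The 70% cut needs 7 of 10, 8 of 11 or 9 of 12.

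| Reading of the form | Score | Class |
|---|---|---|
| Keyed rows only | 8/10 = 80.0% | good |
| 11 items, one unkeyed row dropped, the other not credited as true | 8/11 = 72.7% | good |
| 11 items, unkeyed rows true, one true row dropped | 9/11 = 81.8% | good |
| 12 rows, unkeyed rows true | 10/12 = 83.3% | good |
| 12 rows, neither unkeyed row true | 8/12 = 66.7% | satisfactory |
| 11 items, neither unkeyed row true, one keyed true row dropped | 7/11 = 63.6% | satisfactory |

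The last two readings require both unkeyed statements to stay in the denominator and neither to be true, which is not how they read.

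**Step 3. See what the total score still separates.** Take 11 items, 9 true and 2 false. A fully informed resident scores 11, one who always agrees scores 9, and one who always answers 'don't know' scores 0. The first two differ by 2 points (2/11 = 18 percentage points) and share the same class. The third is correctly classed as poor.

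**Step 4. Allow for 'don't know'.** Suppose a resident with no knowledge uses 'don't know' on a share of items and answers 'true' to 80% of the rest (both are assumptions). The chance of reaching 8 of 11 is 55% with no 'don't know' answers, 12% with 25%, and 1% with 50%. Misclassification therefore depends heavily on how freely residents admit not knowing.

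**Step 5. Gain without learning, present key (9 true, 2 false) against a 6/5 key.**

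- If a share d of all items moves from 'don't know' to an uninformed 'true', the expected gain is 9d now and 6d under 6/5. At d = 0.3 (assumed) that is 2.7 against 1.8 points, a cut of one third.
- If the share d moves from 'false' to 'true', the expected gain is (9 − 2)d now and (6 − 5)d under 6/5. At d = 0.3 that is 2.1 against 0.3 points.

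**The case against.** A reader might infer that the knowledge score cannot separate learning from agreeing at all. The documents do not support that: items 7 and 11 are keyed false, and 'don't know' is printed on every row and earns nothing.

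A reader might also infer that the arm comparison is biased. That is not shown. Both arms complete the same form at the same times, residents of either arm who cannot read are interviewed, and agreeing that is equal in both arms does not by itself produce an arm difference. The encouragement in section 3.7.1 concerns performing foot care, not answering questions. The bands also appear peripheral to the test: n (%) is listed under the descriptive objective in Table 3.5, and no between-arm test of the classes is stated.

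Finally, the form is a draft. It goes to six content experts and a pilot and is then revised (section 3.7.1).

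All of this limits the point without removing it. The planned reviews do not name key balance, so nothing in the plan ensures that the draft is corrected on this account.

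**Conclusion.** The point holds for the classification and, more weakly, for the total. On the natural readings of Part F, agreeing with everything earns about 73% to 83% and the label good. The total leaves two points between an all-agreeing and an informed resident. This rests on the printed key and on reading the two unkeyed rows as true.

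Equal agreeing in both arms would inflate the reported good percentages and leave an all-agreeing resident at most 2 points to gain. A larger rise in the intervention arm would appear as a knowledge gain, but that rise is plausible rather than demonstrated.

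It would also be wrong to expect a balanced key to remove almost all of the spurious gain. The fall from 2.1 to 0.3 points applies only to moves from 'false' to 'true'. For moves from 'don't know' to 'true', the reduction is about one third.

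This is a minor matter affecting one secondary outcome. It is worth correcting because the correction is cheap.

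**What to change.** First settle the item count and the two missing keys, which are separate defects. Then, before the pilot, reword three or four of the 'true' statements as false ones, in plain language without double negatives, to reach about 6 true and 5 false. Mix the order. Keep the one-point scoring and the 70% and 50% cut-offs, and check comprehension of the reworded items in the pilot.

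Ticking 'true' throughout then scores 6/11 = 55%, which is satisfactory and no longer good. The gap to a fully informed resident widens from 2 to 11 − 6 = 5 points.

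The cost is small. The scale is the study's own, and expert review, translation and piloting are still planned. The downside is that false statements may be slightly harder for residents with little schooling. Making the change after baseline would break comparability across the three time points, so it should be made now.

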### **3.6.2 Quality control**

#### **3.6.2.1 Validity and Reliability of the instruments**

Measurement of the validity and reliability of the instruments and the intervention program are major concern in any research. The measurements of these instrument and intervention program represented the concept or aim of research questions; otherwise any conclusions drawn from this study was invalid.

Three instruments used in this study was adapted from previous study. The Neuropathy and Foot Ulcer Specific Quality of Life (FS-QOL) (Vileikyte et al., 2003), The Foot Care Confidence Scale (FCCS) (Sloan, 1998) and The Diabetes Foot Self-

Care Behaviour Scale (DFSBS) (Chin & Huang, 2013) has been tested for the instrument validity previously. Table 3.2 shows the validity and reliability of the instruments adapted in this study.

Table 3.2 The description about adapted instrument used in this study

| Instrument                                                                        | Validity and reliability                                                                                                                                 | Approval                                                                         |
|------------------------------------------------------------------------------------------|-----------------------------------------------------------------------------------------------------------------------------------------------------------------|-----------------------------------------------------------------------------------------|
| The Neuropathy and Foot Ulcer Specific Quality of Life (FS-QOL) (Vileikyte et al., 2003) | The instrument revealed three physical symptom measures and two psychosocial functioning measures with good reliability (alpha 0.86–0.95)                       | Permission has been granted from the original researcher via email prior to this study. |
| The Foot Care Confidence Scale (FCCS) (Sloan, 1998)                                      | The FCCS had a Cronbach's alpha of 0.92 and the instrument is a practical to be used in many settings (Sloan, 1998).                                            | The instrument is a public domain                                                       |
| The Diabetes Foot Self-Care Behaviour Scale (DFSBS) (Chin & Huang, 2013)                 | Internal consistency was acceptable (Cronbach's alpha = 0.73), and interclass correlation coefficient for test retest reliability over a 2-week period was 0.92 | Permission has been granted from the original researcher via email prior to this study. |

In this study, the researcher will prepare the questionnaire in two languages; English and Malay. The English questionnaire will be translated into the Malay version. The English version of the questionnaire will be sent to Institute Terjemahan dan Buku Malaysia (ITBM) for translation process. Basically, the first stage involved the forward translation by bilingual translator independently translating the instrument from English into Malay. After that, another translator who had not seen the original questionnaire translated the new translation back into the English language. This technique called semantic translation and the translators are from person who has medical and health sciences background.

Validity and reliability for the development intervention program and instrument of knowledge on foot care scale and foot care outcome expectation scale will be tested and piloted prior to main study. The validity of the intervention program and instruments will be tested using face and content analysis. The materials will be given to a panel of experts; consisting of supervisors, endocrinologist, diabetic nurse educator, foot care nurse and elderly with diabetes to ensure the questions are appropriate and relevant in our current practice, setting, culture and population.

Content of the intervention program and the instruments will be judge by expert panels. The purpose of it is to verify that all the items and concepts measured are representative, well defined and reviewed with an appropriate weighing to the elderly population. Content Validity Ratio (CVR) =  $(2n_g / N) - 1$ , will be used for validity conformity. Where  $n_g$  is the number of Subject Matter Experts (SMEs) who think the item is good and  $N$  is the total number of SMEs. In this approach, a panel of SMEs is asked to indicate whether or not a measurement item in a set of items is "essential" to the operationalization of a theoretical construct (Johnston & Wilkinson, 2009). "Essential" items or assessment tasks are ones that best represent the goal and are desired. The value lies between -1.00 to +1.00, where a CVR = 0.00 means that 50%

of the SMEs in the panel size of N believe that the portfolio task is essential thereby valid (Johnston & Wilkinson, 2009).

The reliability will be tested with internal consistency. Reliability of result was tested using Cronbach's alpha test after the pilot study is conducted. The reliability coefficient (alpha) can range from 0 to 1, with 0 representing an instrument with full of error and 1 representing total absence of error. A reliability coefficient (alpha) of 0.70 or higher is considered acceptable reliability (Aday & Cornelius, 2006).

Factor analysis will be performed to examine interrelationships among the large number of variables and disentangles those relationships to identify clusters of variables that are most closely linked together (factors) (Grove, Burns & Gray, 2012). The responses to the instrument items will be subjected to principal component analysis to identify underlying dimensions or factors. A threshold of 0.60 will be used to determine which statements are considered to be part of a factor. Internal consistency for each factor, as measured by Cronbach's alpha is acceptable as the alpha values for all the factors are above 0.80.

### **3.6.2.2 Pilot Study**

Pilot study is a miniature of the proposed study. Pilot study will be conducted to identify and investigate the feasibility of the suggested study and to detect any possible errors in the data collection instruments such as any ambiguous words and instructions, inadequate time and to confirm whether the variables defined by the operational definitions were actually measurable and observable (Brink, 2006; Polit & Beck, 2006).

This pilot study will be conducted on XXX to XXX involves 10% (XXX) of the population targeted. Respondents involved in pilot study will be excluded from the real study. This will be done to check the understanding of questionnaire given to the respondents. A part from that, the pilot study is to identify the feasibility of data collection procedures, completed time and the administration of the questionnaire for clarity and respondent's willingness to complete it. The results from this pilot study will provide some indication of anticipated problem that may arise in the research study.

Approximately at about 30 minutes is needed for respondents to complete the questionnaire. Any changes to the items of instrument will be testing for reliability using Cronbach's alpha test to detect the internal consistency or reliability acceptable results.

All the participating patients will be interviewed at the end of the pilot program. They will be asked for their opinion on the practicability and expected effectiveness of the education program. Practicability is defined here as the degree to which the various parts of the program can be carried out and fitted into the present way of working. The expected effectiveness will be described as the extent to which the participants expected the program to contribute to improving foot self-care behaviour for diabetes management.

